## Abstract

**Background::**

Newborn infants admitted to the neonatal intensive care unit require arterial cannulation for hemodynamic monitoring and blood sampling. Arterial access is achieved through catheterization of umbilical or peripheral arteries. Peripheral artery cannulation is performed in critically ill newborns, but artery localization and cannulation is often challenging and unsuccessful. Therefore, increasing the internal diameter and preventing vasospasm are important for successful peripheral artery cannulation in neonates. Topical glyceryl trinitrate has the potential to increase cannulation success by relaxing arterial smooth muscles and thus increasing the internal diameter. We aim to conduct a pilot randomized controlled trial to evaluate the efficacy and safety of topycal glyceryl trinitrate in increasing the diameter of the radial artery in neonates.

**Methods/Design::**

This study will be a single-center, observer-blind, randomized, placebo-controlled trial conducted in the neonatal intensive care unit of Perth Children's Hospital, Western Australia. A total of 60 infants born at >34 weeks of gestation who are admitted for elective surgery or medical reasons and for whom a peripheral arterial line is needed for sampling or blood pressure monitoring will be recruited after informed parental consent is obtained. The primary outcome will be the change in radial arterial diameter from baseline to postintervention. Secondary outcomes will be the absolute and percentage change from baseline in the radial arterial diameter in both limbs and safety (hypotension and methemoglobinemia).

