#### Trial hypothesis being tested:

The topical application of GTN for 30 - 60 minutes increases the radial artery diameter compared to no application.

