### Interventions

Glyceryl trinitrate 5mg (Transiderm-Nitro patch, 5mg/24 hours) will be applied for 30 minutes, 45 minutes or 60 minutes. Neonates will be allocated to either the GTN Group or the Control Group. Glyceryl trinitrate is a registered medication in the Australian Therapeutic Goods Registry. The Therapeutic Goods Administration (TGA) has been notified about this clinical trial (Reference number: CT-2023-CTN-02133-1).

GTN Group: for neonates in this group, a GTN patch (5mg) will be applied at the site of radial artery cannulation for 30 minutes (Group A, n = 15), 45 minutes (Group B, n = 15) or 60 minutes (Group C, n = 15). Immediately after its application, the GTN patch will be covered with a Coban™ adhesive bandage to ensure blinding.

Control Group: for neonates in this group (Group D, n = 15), a Coban™ adhesive bandage with no intervention will be applied to the bare skin at the site of the radial artery for 30 minutes (n = 5), 45 minutes (n = 5) or 60 minutes (n = 5) to ensure blinding.

Only one arterial site per infant will be studied to ensure that the samples are independent.

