### Study endpoint

The primary endpoint of the study is radial artery diameter. After obtaining informed consent from a patient's parent, images of the radial artery will be obtained from the infant's wrist using a portable ultrasound machine. The diameter of the radial artery will be measured using a linear, high-frequency hockey stick probe (6 - 113MHz) with the Philips EPIQ CVx Diagnostic Ultrasound system.

Measurements will be obtained in the short-axis plane of the distal forearm, medial to the border of the styloid process of the radius and at the point with maximal pulsation of the radial artery, with the wrist at a 45º angle.^(16)^ The point will be marked to guide the intervention and ensure coverage of the site over the peripheral artery, which will be measured postintervention. The operator will be an experienced neonatologist blinded to the study group. Measurements will be obtained in both radial arteries at baseline before application of the GTN patch/bandage with no patch and at 30 minutes, 45 minutes or 60 minutes after application.

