### Outcomes

#### Primary outcome:

the primary outcome will be the change in the postintervention radial artery diameter from baseline. This will be compared between the GTN and Placebo Groups.

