#### Unblinded staff:

a nursing staff member who is not involved in the day-to-day management of the neonate will be responsible for opening the envelope, determining the group assignment and applying the GTN patch/placebo and removing the GTN patch/placebo with no additional participation in the study.

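### The trial is labelled placebo-controlled but controls receive only a bandage on bare skin, and nothing described keeps the two groups' skin alike when the operator re-scans the uncovered site

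*Protocol article*

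**What the plan says.** **Placebo wording.** The abstract (Methods/Design) describes an "observer-blind, randomized, placebo-controlled trial". Under Primary outcome, the change in diameter is the comparison of interest: "This will be compared between the GTN and Placebo Groups". The Unblinded staff paragraph gives a nurse the task of "applying the GTN patch/placebo and removing the GTN patch/placebo". Table 3, in the primary-outcome row, refers to a glyceryl trinitrate or placebo patch.

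**What controls receive.** In the Interventions section, the Control Group gets an "adhesive bandage with no intervention will be applied to the bare skin at the site of the radial artery". Table 1 likewise describes the control covering as a bandage without a patch. The trial hypothesis is that GTN "increases the radial artery diameter compared to no application". No dummy patch is described anywhere in the article.

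**Masking.** In the GTN groups, "the GTN patch will be covered with a Coban™ adhesive bandage to ensure blinding". Table 1 lists removal of the covering by unblinded nursing staff, and then the post-intervention ultrasound by a blinded operator. The Study endpoint section fixes where that scan is made: "The point will be marked to guide the intervention and ensure coverage of the site over the peripheral artery, which will be measured postintervention". Operator blinding is stated in several places (Table 1, Study endpoint, Blinded staff, Data collection methods, Statistical methods). The measures described in support are the bandage and the use of a separate nurse.

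**The concern.** There are two parts, of different strength.

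The first is a contradiction within the article. A placebo control is a specific design property: the comparator resembles the active product and differs only in the drug. Here the control condition is a bandage with nothing beneath it. A reader of the abstract, or a later meta-analyst coding the design, would credit the trial with a feature it lacks.

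The second is a gap in the masking of the primary outcome. The bandage hides the patch while both are on. At the second scan the covering is off, and the operator works on skin that carried a patch in GTN infants and only the bandage in controls. If the patch leaves any trace, the operator can tell the groups apart at the moment the outcome is recorded.

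The outcome is an ultrasound diameter in an artery assumed to average 0.76 mm, so a small systematic difference in measurement would look the same as a drug effect. Adjusting for baseline would not remove it, because it enters only at the second scan. The contralateral limb would not expose it either, because that limb is never covered.

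**Working it through.** **Step 1: the comparator, place by place.**

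| Place in the article | Comparator as described |
|---|---|
| Abstract, Methods/Design | placebo |
| Primary outcome | placebo group |
| Unblinded staff | placebo |
| Table 3 | placebo patch |
| Trial hypothesis | no application |
| Table 1 | bandage, no patch |
| Interventions, Control Group | bandage on bare skin, no patch |

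The first four and the last three cannot all be right.

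**Step 2: the sequence at the site.** The point is marked and scanned at baseline. It is then covered by patch plus bandage, or by bandage alone. A nurse with no other study role uncovers it, and the operator re-scans the same point. Concealment by the bandage ends before the outcome is measured. From there, blinding depends on the skin looking the same in both groups, and the article describes nothing that would make it so.

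**Step 3: the plan's own power figure.** Inputs from Sample size: 4 groups of 15, SD 0.18 mm, difference 0.19 mm, alpha 0.05. Suppose all three GTN means lie a distance d above control. The grand mean is then 0.75d above control, and the sum of squared deviations is (0.75d)² + 3(0.25d)² = 0.75d². The noncentrality is

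λ = 15 × 0.75d² / 0.18² = 11.25d² / 0.0324.

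For d = 0.19, λ = 12.5. With 3 and 56 degrees of freedom the power is 83.0%, which agrees with the plan's claim of more than 80%. Also, 0.19/0.76 = 25%, as stated.

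**Step 4: what a reading shift would do if there were one.** Set the true effect to zero and add an assumed shift b to the second reading in all 45 GTN infants. For the ANOVA, use λ above with d = b. For the pooled comparison of 45 with 15 (two-sided t, 58 df):

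- SE = 0.18 × √(1/45 + 1/15) = 0.0537 mm
- noncentrality = b / 0.0537

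| Assumed shift b | Share of 0.19 mm | λ | Four-group ANOVA | Noncentrality (t) | 45 versus 15 |
|---|---|---|---|---|---|
| 0.02 mm | 11% | 0.14 | 5.8% | 0.37 | 6.6% |
| 0.05 mm | 26% | 0.87 | 10.2% | 0.93 | 15.0% |
| 0.10 mm | 53% | 3.47 | 29.5% | 1.86 | 44.9% |

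The percentages in the ANOVA and 45-versus-15 columns are false-positive rates, against a nominal 5%.

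Both analyses are shown because Sample size powers a four-group ANOVA, while the primary outcome is worded as a comparison of two groups. The 0.18 mm is an SD of diameters, not of changes, and the article gives no SD for the change. A smaller change SD would make a given shift more harmful. At an assumed 0.13 mm (a baseline-to-post correlation of about 0.74), shifts of 0.05 and 0.10 mm give 15.7% and 53.4% for the ANOVA, and 24.5% and 71.8% for the pooled test.

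**The case against.** The strongest reply is that unblinding is not documented. No section says the patch leaves an outline, residue or redness. Both groups wear the same type of bandage for 30, 45 or 60 minutes, so marks from the bandage itself would appear in both. The nurse who applies and removes the covering takes no other part in the study, and blinded and unblinded duties are logged separately. Statistical methods mentions a blinded examiner as well as the operator, and Data management says images are stored, so a separate masked reading is possible. Site cleaning is the sort of detail a condensed article leaves to the full protocol.

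Most of this stands, and it limits the second part of the point to a risk. It does not remove that risk. The separate nurse keeps the operator from seeing the patch but does not make the skin look alike, and the article does not say that the examiner reads images independently. The absence of a dummy is not an omitted detail, since the article states positively that the control bandage goes on bare skin.

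Some stronger readings are tempting but not supported:

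- A reader might infer that the operator will be unblinded, or that the observer-blind label is false. That label requires only that the observer not know the allocation, and nothing in the text contradicts it. Only the placebo label conflicts.
- A reader might take the error rates above as the trial's actual error. They rest on shifts that have no source in the documents.
- A reader might use the 6.7 cm² in the dose justification as the footprint of the trial patch. It is given for a differently named product.
- A reader might add that the bedside nurse or family could see or feel the patch under the bandage. The article gives no basis for this, and it does not bear on the ultrasound reading.

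**Conclusion.** The contradiction is certain. Four places describe a placebo or placebo patch, three describe a bandage with no patch, and the stated placebo control is not part of the design.

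The weakness in masking the primary outcome is an inference from the order of events: cover off, then re-scan of the same marked point. It depends on the patch leaving some visible trace, which the documents neither state nor rule out, and removal by a separate nurse is a partial safeguard. If a trace did lead to a shift of 0.05 mm, the 5% error would be about 10% or 15% depending on the analysis, and 0.10 mm would give about 30% or 45%. A shift of 0.02 mm would hardly matter. These figures assume no true effect, SD 0.18 mm and the same shift in every GTN infant. They show how sensitive the measurement is, not that bias is present.

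The wording should be corrected in any case. The masking is worth strengthening because the remedy is small.

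**What to change.** Preferred: under the control bandage, place an inert adhesive dressing of the same size and outline as the patch actually used in the trial. Have the unblinded nurse remove the covering and clean the skin in the same way in both groups before the operator returns. The placebo wording would then be close to true, with the hypothesis, Table 1 and the Interventions section reworded to match. The cost is a short amendment, 15 dressings and adhesive contact for 15 control infants.

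If no dummy dressing is used, replace the placebo and placebo-patch terms with a no-patch bandage control in the abstract, Primary outcome, Unblinded staff and Table 3. Also have the stored images read masked to group where this needs no extra staff. Masked reading protects the measurement taken from the image but not the acquisition of the image, so it is the weaker option. It spares control infants the adhesive contact.

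In either case, add one sentence saying how the operator stays blinded once the site is uncovered.

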**Discussion::**

This will be the first randomized controlled trial evaluating the use of topical glyceryl trinitrate to facilitate peripheral artery cannulation in neonates. If our pilot randomized controlled trial confirms the benefits of glyceryl trinitrate patches, it will pave the way for large multicenter randomized controlled trials in this field.

## INTRODUCTION

Children admitted to intensive care units (ICUs) require arterial cannulation for hemodynamic monitoring and blood sampling. In neonates, arterial access can be achieved through umbilical artery catheterization in the first 3 - 4 days of life, whereas in older infants and children, it is achieved via peripheral arteries. Even in neonates, umbilical arterial catheterization may not be feasible (e.g., in neonates with abdominal surgical conditions and omphalitis). The radial, posterior tibial, and brachial arteries are commonly used for cannulation in children and neonates. Radial artery cannulation is also used for percutaneous cardiac intervention. Radial arteries are of small caliber, which makes their localization and cannulation challenging and potentially unsuccessful. The radial artery is the most frequently used site for cannulation, as it is superficial and has a relatively large diameter compared to other peripheral arteries. Repeated cannulation attempts can lead to bleeding, spasm and dissection of the peripheral arteries.^(1)^ Ultrasound-guided insertion can increase cannulation success but requires high expertise.^(2,3)^ A recent pediatric audit found that even with ultrasound, the first attempt success rate was only 31%.^(4)^ Resource-limited settings may be limited by the cost of ultrasound equipment and maintenance. Therefore, increasing the internal diameter and preventing vasospasm are important for successful peripheral artery cannulation in neonates.

The use of glyceryl trinitrate (GTN) as a local application has the potential to increase cannulation success by increasing the diameter of peripheral arteries and preventing vasospasm. Glyceryl trinitrate is converted to nitric oxide in vascular smooth muscle, which activates guanylate cyclase and increases the level of cyclic guanosine monophosphate. This relaxes arterial smooth muscle, leading to vasodilation.^(5)^ Adult studies have shown that locally applied GTN increases the internal diameter of peripheral arteries, improves the success rate of cannulation, and reduces the risk of vasospasm and occlusions during cardiac catheterization.^(6-8)^

Our recent systematic review^(9)^ found only two studies addressing this issue in the pediatric population. One study used a topical patch of GTN^(10)^, while the other study used subcutaneous GTN.^(11)^ Both studies found that local GTN improved the success rates and shortened the time taken for arterial cannulation. However, the sample size was very small. Moreover, the neonatal population was not represented in these studies.

We hypothesize that the local application of GTN in the form of a transdermal patch would achieve adequate dilation of the radial artery and increase the first-attempt success rate of peripheral artery cannulation in neonates.

We aim to conduct a pilot randomized controlled trial to evaluate the efficacy and safety of local GTN in increasing the diameter of the radial artery in neonates.

## Methods/Design

### Aim and hypothesis

We aim to conduct a randomized controlled trial to establish the effectiveness of local GTN in increasing the diameter of the radial artery in neonates.

We hypothesize that local application of GTN in the form of a transdermal patch will result in adequate dilation (by at least 25% from the baseline diameter) of the radial artery in neonates.

### Objectives

The specific objectives are:

To confirm that GTN patch application for 30 - 60 minutes increases the radial artery diameter of neonates.To confirm that it is safe to apply a GTN patch for 30 - 60 minutes for neonates.To estimate the mean values of the within-patient changes in the peripheral artery diameter from baseline to inform the choice of the optimal duration of GTN patch application in the context of cannulation in neonates.To evaluate the feasibility of a proposed future trial design to assess the impact of GTN patches on first-attempt cannulation rates in terms of recruitment and data collection.

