### Exclusion criteria

Neonates who undergo previous radial artery cannulation attempts and those who have hematomas at the cannulation site, abnormal Allen's test results, a hypercoagulable state, coagulopathy, and peripheral vascular disease.Neonates with unstable vital signs, including hypotension, shock or significant arrythmias.Neonates scheduled to undergo cardiac surgery.Neonates with increased intracranial pressure, intracranial hemorrhage, and recent use of sildenafil.Neonates with a visible deformity in the radial artery area.

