### Sample size

We aim to recruit 60 patients (15 in each arm: 1 control and 3 GTN arms) over 12 months, which is achievable given that we expect approximately 250 eligible patients to be admitted to the neonatal ICU each year.

Justification of the sample size is based on the desire to demonstrate that reasonable vasodilation with GTN patch application is achievable in our target study population. We assume that the measures of the radial artery diameter in study participants will have a mean of 0.76mm without treatment and a common within-group standard deviation of approximately 0.18mm, as observed in a reference study of neonates aged 0 - 6 months.^(12)^ With a sample size of 15 for each group (1 control and 3 GTN patch groups), the margin of error around the corresponding estimated population mean diameters is less than 1 mm, and an omnibus one-way ANOVA would have more than 80% power to determine whether GTN patch application increases the radial artery diameter when the minimum mean of the treatment group differs from that of the control group by approximately 0.19mm (alpha = 0.05). Analyses based on the change from baseline, which is our primary outcome, are expected to be more powerful than analyses assessing the cross-sectional diameters, and the detectable cross-sectional difference of 0.19mm corresponds to an approximate 25% increase from the estimated baseline value, which is of the order previously observed in children aged 0 - 2 years receiving subcutaneous injections of GTN,^(11)^ and substantially less than that observed after patch application in children aged 2 - 8 years (average increase of 40% in the radial artery diameter after 30 minutes and an increase of 70% after 1 hour).^(10)^ Furthermore, power will be increased by extending the assessment of GTN-induced vasodilation to an ANCOVA that reduces residual variation by adjusting for key demographic/clinical correlates of arterial diameter.

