### Statistical methods

Table 3 gives a description of the timing and method of assessment of the efficacy and safety parameters. The ultrasound operator and examiner will be blinded to the study.

**Table 3 t3:** Timing and method of assessment of the efficacy and safety parameters

		Measured by	Analysis
Primary efficacy outcome			
	Change in postintervention ipsilateral radial arterial diameter from baseline	Ultrasound at the site of cannulation measured at time of randomization of glyceryl trinitrate/placebo patch and 30, 45 or 60 minutes postintervention	ANCOVA
Secondary outcomes			
	Cross-sectional radial artery diameter in the ipsilateral limb	Measured postintervention by ultrasound	Linear regression
	Percentage change from baseline in radial arterial diameter in ipsilateral limb	Ratio of the postintervention to baseline radial arterial diameters as measured by ultrasound	Linear regression
	Change in the radial artery diameter in the contralateral (no intervention) limb from baseline	Difference and ratio of the radial artery diameter measured at baseline and postintervention	Mixed effects regression modeling of radial artery diameters in both limbs.
Safety outcomes			
	Blood pressure	Systolic blood pressure monitored every 15 minutes	Mixed effects regression modeling of patient trajectories
	Methemoglobinemia	Monitoring of the oxygen requirement and a blood gas analysis if the oxygen requirement increases	Mixed effects regression modeling of patient trajectories

ANCOVA - Analysis of covariance.

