## DISCUSSION

Given the importance of having reliable arterial access in neonates and the difficulty in cannulation, any intervention that improves the chances of successful peripheral arterial catheterization will help improve the clinical outcomes of critically ill neonates. This research project will help determine if the topical use of GTN for peripheral artery cannulation is beneficial and whether its benefits outweigh the potential side effects. This will be the first study evaluating the use of topical glyceryl trinitrate to facilitate peripheral artery cannulation in neonates. If our pilot RCT confirms the benefits of the GTN patch, it will pave the way for large multicenter RCTs evaluating its efficacy in improving the first-attempt success rate of peripheral artery cannulation in neonates.

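### Objective 2 promises to confirm that the GTN patch is safe, but 45 exposed infants can at best bound the risk at about 8%, and Table 3 names no analysis of event incidence

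*Protocol article*

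**What the plan says.** The Objectives section lists four aims. The second is "To confirm that it is safe to apply a GTN patch for 30 - 60 minutes for neonates". The third and fourth use softer verbs, estimating and evaluating.

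On numbers, the Sample size section states: "We aim to recruit 60 patients (15 in each arm: 1 control and 3 GTN arms) over 12 months". Interventions and Table 2 give the same split: three GTN durations of 15 infants, so 45 exposed, and 15 controls. The rationale for that number concerns efficacy alone: "Justification of the sample size is based on the desire to demonstrate that reasonable vasodilation with GTN patch application is achievable". No acceptable event rate, safety margin or target precision for a safety estimate is given.

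Data and safety monitoring treats the key safety outcomes as events per infant: hypotension, meaning a systolic fall of at least 30% from baseline, and methemoglobinemia on blood gas. The monitoring committee reviews them after 20 and 40 participants. In Statistical methods, Table 3 gives one analysis for both blood pressure and methemoglobinemia: "Mixed effects regression modeling of patient trajectories".

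Elsewhere the article is more cautious. The Introduction describes a pilot that will evaluate efficacy and safety, and Safety outcomes says side effects will be assessed.

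**The concern.** An objective to confirm safety needs two things: a statement of what risk would be acceptable, and enough exposed infants to exclude a risk above it. The article gives neither. The number of infants was chosen for a difference in diameter, and its power says nothing about uncommon adverse events.

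The named analysis does not fill the gap. A mixed-effects model of blood pressure describes average change over time. It does not report how many infants had a 30% fall, or how high the true proportion could be.

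At stake is what the trial may conclude. If few or no events occur, objective 2 as worded invites the conclusion that safety is established, and Table 3 provides no incidence or upper limit to temper it. The planned larger trials would then start from a safety statement stronger than the data support.

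**Working it through.** **Inputs.** 15 infants per arm, four arms, 45 on GTN (Interventions, Sample size, Table 2). SD 0.18 mm, difference 0.19 mm, alpha 0.05, power above 80% (Sample size). The article gives no figure for safety.

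**The plan's own figure.** One-way ANOVA, 4 × 15, all three GTN means 0.19 mm above control:

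- Grand mean = 3 × 0.19 / 4 = 0.1425 mm above control.
- Noncentrality = 15 × (0.1425² + 3 × 0.0475²) / 0.18² = 15 × 0.027075 / 0.0324 = 12.5.
- Power on 3 and 56 degrees of freedom = 0.83.

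The efficacy statement is reproduced and is not in question here.

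**Best case for safety: no events.** The exact (Clopper-Pearson) upper limit for 0 events in n infants is 1 − 0.025^(1/n) for a two-sided 95% interval and 1 − 0.05^(1/n) for a one-sided one.

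| Infants | Two-sided 95% | One-sided 95% |
|---|---|---|
| 45 (all GTN) | 1 − 0.025^(1/45) = 7.9% | 1 − 0.05^(1/45) = 6.4% |
| 15 (one duration) | 1 − 0.025^(1/15) = 21.8% | 1 − 0.05^(1/15) = 18.1% |

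The choice of convention does not change the message. Any observed event raises these limits.

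**Chance of a trial with no events**, (1 − p)^n. The true risks p are illustrative assumptions; the article states none.

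| True risk | None in 45 | None in 15 |
|---|---|---|
| 2% | 40% | 74% |
| 5% | 10% | 46% |
| 10% | 0.9% | 21% |

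**Infants needed to exclude a given risk with no events**, n ≥ ln(0.025) / ln(1 − p), again for assumed thresholds: 72 for 5%, 183 for 2%, 368 for 1%. The 45 exposed infants fall short of all three.

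**Why the trajectory model does not answer the question.** Suppose, as an illustration, that 2 of 45 GTN infants have a 30% systolic fall and the rest do not change. The incidence is 2/45 = 4.4%, yet the mean fall is 2 × 30% / 45 = 1.3%. A near-flat average trajectory is compatible with events of the kind the monitoring committee is asked to count. For methemoglobinemia, Table 1 lists a gas after the intervention and Table 3 a gas only if the oxygen requirement rises. Neither describes a series of methemoglobin values per infant to which a trajectory could be fitted.

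**The case against.** The strongest reply is that this is one verb in a trial that otherwise calls itself a pilot. The stated trial hypothesis concerns diameter only, no safety test is attached to objective 2, and other sections say evaluate or assess. That stands, and it fixes the size of the point: the objective is out of line with the rest of the article, and the design itself is not shown to be wrong.

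A second reply is that event counts with intervals are routine content for an analysis plan that is not shown, and that the monitoring committee will count events anyway. This holds only in part. Table 3 is not silent: it names a method for each safety outcome, and that method does not match the event definition. Interim review after 20 and 40 infants does not replace a final estimate. A fitted blood pressure model could be made to predict the proportion crossing 30%, but only through assumptions about the tail of its distribution, and the article does not propose this.

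A reader might also infer more than the text supports:

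- **That the Discussion promises a benefit-risk verdict.** It says only that the project will help determine "whether its benefits outweigh the potential side effects". That is already hedged and can stay.
- **That the exclusions are a flaw.** Leaving out "Neonates with unstable vital signs, including hypotension, shock or significant arrythmias" is a visible eligibility choice. It defines whom the safety estimate describes; it is not an error.
- **That 21.8% is the headline figure.** Objective 2 treats 30 to 60 minutes as one range, so the pooled 7.9% is the closer match. The per-duration figure is supporting context, relevant because objective 3 looks ahead to the choice of duration.
- **That the investigators will declare the patch safe if no event occurs.** The article does not say so.

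**Conclusion.** The point holds as an overstated objective paired with a safety analysis that does not estimate the defined events. It should be corrected, but it does not call for a larger trial and leaves the primary analysis untouched.

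In the most favourable outcome, a true risk of up to 7.9% across all GTN infants stays compatible with the data, and up to 21.8% in any one duration arm (exact two-sided 95%). Whether 7.9% would be tolerable cannot be judged from the article, because it sets no acceptable risk.

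The limits assume that all 45 GTN infants are enrolled and assessed for both events. Withdrawals would widen them. So would measuring methemoglobin only in infants whose oxygen requirement rises, if the others are not counted as assessed.

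**What to change.** 1. Reword objective 2, for example: to estimate the incidence of hypotension (as defined under Data and safety monitoring) and of methemoglobinemia during 30 to 60 minutes of GTN patch application in hemodynamically stable infants born at >34 weeks. This agrees with the verbs already used in the Introduction and in Safety outcomes.
2. In Table 3, add for each event the number and proportion of infants affected, with an exact 95% confidence interval: pooled GTN as the primary safety estimate, each duration as descriptive, and control. Infants removed from the study because of an event count as having had it.
3. Keep the blood pressure trajectory model as a complement, since it describes average change.

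The Discussion sentence and the exclusion criteria need no change. The cost is the wording of one objective and an addition to the safety rows of one table, with no extra infants or procedures. The downside is a less favourable safety claim: an incidence with an upper limit in place of confirmed safety.
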